### Trial medicines

The Investigational Medicinal Product for this trial will be Prednisolone 20 mg oral tablets (×10), procured from GALEN Pharma GmbH (Kiel, Germany). Placebo tablets will be manufactured by Piramal Healthcare Ltd (Morpeth UK) to exactly match the prednisolone tablets in dimensions, appearance and taste, to maintain allocation blinding.

A relatively high dose of corticosteroids has been selected in order to maximise the probability of detecting a treatment effect (that is, an ‘efficacy’ dose) such that a negative result cannot be criticised for being due to an inadequate dose. The patient’s weight and height will be recorded in order to allow us to take account of dose effects.

### Recruitment sites

A minimum of 60 GP practices will be recruited to take part in the trial across the four trial centres, with a wide geographical spread in both urban and rural areas across the South West, Midlands and North West of England. The number recruited will take account of anticipated ready to recruit (open) to actually recruiting (active) ratios. Participating practices are required to have recent (within 5 years) Good Clinical Practice (GCP) training for all practice staff who will be confirming patients’ eligibility, authorising the trial prescription, consenting patients or entering clinical data onto the online database.

### Research ethics and governance

Multi-centre approval was granted by the Central Bristol Research Ethics Committee (Ref: 12/SW/0180) and by the MHRA (EudraCT number: 2012-000851-1). The lead Research and Development organisation was the Western (now West of England) Clinical Research Network. The following Clinical Commissioning Groups provided Research and Development approval for OSAC trial recruitment at primary care sites within their localities: Bristol (lead Clinical Commissioning Group); Berkshire East; Birmingham CrossCity; Blackburn with Darwen; Bracknell and Ascot; Coventry and Rugby; Cumbria; Dorset; East Lancashire; Fylde & Wyre; Gloucestershire; Hardwick; Kernow; Lancashire North; Leicester City; Nene; North and West Reading; North Derbyshire; North East Hampshire and Farnham; North Hampshire; North Somerset; Northern, Eastern and Western Devon; Nottingham City; Oxfordshire; Portsmouth; Redditch and Bromsgrove; Sandwell and West Birmingham; Somerset; South Devon and Torbay; South Eastern Hampshire; South Warwickshire; Warwickshire North; West Hampshire; Wiltshire; Wokingham.

Please see Additional file 1 (SPIRIT checklist) for a summary of how the protocol meets the recommendations of the SPIRIT (Standard Protocol Items: Recommendations for Interventional Trials) initiative.

### Screening for eligibility (the routine consultation)

Patients presenting with cough will be approached by the healthcare professional managing their clinical care (‘Responsible Clinician’) or by another member of the practice team responsible for patient identification (for example, reception staff or the ‘Recruiting Clinician’), given a short explanation of the trial, and invited to be screened for eligibility. If the patient is willing, the clinician will screen the patient for eligibility. This process includes a detailed check of the inclusion/exclusion criteria, and a routine clinical examination, of which the results and the clinician’s diagnosis will be recorded on the case report form (CRF). The routine clinical management of the patient will be completed as normal. This may include giving the patient a discretionary delayed antibiotic prescription (to be used if the patient’s condition deteriorates after 48 hours or if failing to improve after 7 days) and the discretionary use of a β-agonist (for example, salbutamol). A requirement for immediate antibiotic treatment renders the patient ineligible.

Once the patient’s eligibility is confirmed, the trial prescription will be authorised (by a GCP-trained GP) for redemption (by the Recruiting Clinician, not the patient) against a trial Patient Pack. The patient is then referred to a further interview for full recruitment and trial entry.

### Trial entry (the recruitment interview)

The recruitment interview must take place on the same, or next, day as the routine consultation. Same-day recruitment will be more efficient for many patients who may not wish to return to the GP practice again the following day. Same-day recruitment will also help ensure that participants take the first dose of their trial medication prior to collecting any delayed antibiotic that may have been prescribed for them by their GP, thereby ensuring the validity of antibiotic consumption as one of the secondary outcome measures. Some patients may wish to start taking a treatment on the same day that they visit the GP practice, and in the absence of a trial treatment those patients may be more likely to take antibiotics obtained from a delayed prescription or visited another healthcare provider while waiting for the next day to enter the trial.

However, if the site or patient do not have time for the recruitment interview on the same day, the patient can be recruited on the following working day, if the following conditions are met: the recruitment interview is not deferred to the Monday following a weekend, to reduce the possibility of recruiting patients whose clinical condition has deteriorated significantly since the eligibility assessment was performed; and any delayed antibiotic prescription is post-dated by at least 24 hours after the recruitment interview, to ensure that the patient has the opportunity to take the first dose of their trial medication prior to collecting their delayed antibiotic prescription.

The Recruiting Clinician will take formal written consent, collect the remaining CRF data (including symptoms, signs and respiratory history), issue the patient with the trial medicines and explain how to take them. The patient will also receive a symptom diary, peak flow meter and other materials to fully equip them for the follow-up, and training in how to measure peak expiratory flow and complete the diary.

### Participant follow-up

All follow-up will be managed by the trial team, who will give participants individual support throughout their follow-up period. Participants will complete the symptom diary online or on paper every day for up to 28 days or until symptoms have been completely resolved for two consecutive days (whichever is soonest). As well as recording the severity of their symptoms, completing the symptom diary includes recording peak flow measurements and whether or not any antibiotics have been taken. The patient will also record how many of the trial tablets they took on days 1 to 5, and any adverse effects during the first 7 days.

All participants will be telephoned within the first 2 days of trial entry, and then each week for 4 weeks to support symptom diary completion, collect the daily data they have recorded during the preceding week (to safeguard against potential loss of data if paper diaries are not returned to the trial centre or there are problems with the post), and to collect the weekly data on resource use and quality of life measures. These methods are similar to those successfully used (with <20% attrition) in previous studies [2,5,40,41].

Should the patient’s cough persist beyond 28 days, their permission will be sought to continue with the weekly calls, up to a maximum of 56 days, in order to establish the day on which the patient last scores their cough as “moderately bad”, and the date on which their cough is completely resolved. The 56 day cut-off point has been chosen as a pragmatic cut-off point, in order to establish the date of cough resolution for the majority of participants while taking account of the participant’s research burden, and of the trial resources. The patient will not be asked to complete any further trial paperwork after the initial 28 day period.

Participants will receive thank you vouchers worth £15 during their participation in the trial, as there is systematic review evidence that small monetary tokens increase response rates [42].

A review of participants’ primary care notes will be undertaken by the recruiting primary care site, to record NHS contacts (and their causes), prescriptions, secondary care referrals and any clinical diagnoses of asthma, COPD, whooping cough or lung cancer in the 3 months post-randomisation. This data collection will take place at least 4 months after randomisation to allow for secondary care contacts and test results to be evident in the primary care notes.

See Figure 1 (study flow chart) for a visual representation of the pathway of the trial participant through the trial (presentation, index consultation, baseline recruitment interview, and follow-up).

**Figure 1 Fig1:**
[figure not shown]
**Study flow chart.** A visual representation of the pathway of the trial participant through the trial (presentation, index consultation, baseline recruitment interview, and follow-up). CRF, case report form; LRTI, lower respiratory tract infection.

### Data management

Clinical data will be collected and managed using a secure, web-based system (OpenClinica) which will be developed, hosted and supported by the University of Oxford and validated by the University of Bristol. Patient confidentiality will be maintained at all stages of data collection. Eligible, consented, randomised patients will be identified by the Participant ID number and the Medicine ID number of the allocated Patient Pack. Entry of data into the on-line database will be the default method of data capture; however, paper-based alternatives will be provided in order to accommodate GPs’ individual preferences. Participants will also be given the choice between online and paper data collection: the symptom diary will be made available online, with the exception of the EQ-5D-5L which will be completed by the patient on paper and also collected by the Trial Research Nurse during the weekly telephone calls.

### Analysis

Descriptive analyses will examine the comparability of the intervention and control group at baseline.

#### Analysis of primary outcomes

Analysis and reporting will be in line with CONSORT guidelines [43]. The primary comparative analysis will be conducted on an intention-to-treat (ITT) basis. For all analyses effect estimates will be presented with 95% confidence intervals and *P* values. For the primary analysis missing data will be assumed to be missing at random and excluded from the analysis.

Duration of cough is calculated as the number of days from the index consultation to the last day that the patient scored 3 or higher, where that last day is followed by at least two consecutive days with a score of less than 3. Cox proportional hazards models (adjusting by centre) will be employed to examine differences in time to recovery from moderately bad to worse cough between the two groups. Individuals not recovered at 28 days post-randomisation will be censored at this time point. The assumption of proportional hazards will be checked using Schoenfeld residuals.

Multiple linear regression models (adjusting for centre) will evaluate the effectiveness of steroids in terms of reducing symptom severity (the mean score of six symptoms) on days 2 to 4.

For both primary outcomes models will also adjust for any covariates demonstrating imbalance between the groups at baseline.

Factors associated with missing data (such as demographics and values of primary and important secondary outcome variables at baseline) will be explored and sensitivity analyses conducted (including inverse probability weights or multiple imputation methods, depending on whether outcome data is partially or fully missing).

It is anticipated that not all participants will complete the full course of tablets; hence, in further sensitivity analysis a per-protocol analysis will be performed.

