### Research questions

#### Primary research question

Can the use of oral prednisolone reduce the duration of moderately bad or worse cough and/or the severity of all its associated symptoms on days 2 to 4 post-randomisation by at least 20% when compared to placebo treatment in adults 18 years and over presenting to primary care with acute LRTI?

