### Sample size calculation

Since the distributions of both primary outcome variables (the duration of moderately bad or worse cough and the mean severity score of all its associated symptoms on days 2 to 4 post-randomisation) will be positively skewed, sample size calculations are based on the log-normal distribution.

The mean (standard deviation (SD)) duration of bad or moderately worse cough was taken from a previous study examining the effectiveness of prescribed antibiotics for acute LRTI [5] and estimated as 5.8 (4.1) days. The mean (SD) symptom severity score between days 2 and 4 taken from the same trial was estimated as 2.3 (1.1). Using standard formulae for the mean and standard deviation of a log-normal distribution, this corresponds to 1.555 (SD 0.637) log days (or geometric mean of 4.74 days) for the cough duration outcome and 0.73 (SD 0.454) on the log scale (or geometric mean of 2.08) for the symptom severity outcome.

To account for testing multiple primary outcomes a lower alpha was specified for the symptom severity outcome to ensure that the overall alpha for the two primary outcomes remains close to 5%. Moderately bad or worse cough has been shown to resolve within 7 days for 50% of patients, 14 days for 75% and 4 weeks for 90% of patients [5]. Therefore, since duration of cough lasts significantly longer than the period during which severity of symptoms are measured (days 2 to 4) and is capturing an element of the illness severity, duration of moderately bad or worse cough might be viewed as the slightly more clinically important outcome. For this reason alpha remained at 5% for duration of cough and was reduced to 0.1% for symptom severity.

Sample size was calculated based on a 20% reduction in the duration of cough, corresponding to a geometric mean in the active treatment group of 3.79 days (mean 1.333 log days). Allowing (conservatively) for 20% attrition, 218 participants will need to be randomised per arm to retain 174 at follow-up and achieve 90% power with a two-sided alpha of 0.05. Hence a total sample size of 436 is required.

For the symptom severity outcome, a final achieved sample size of 174 participants in each arm will provide 89% power to detect a reduction in symptom severity score between days 2 and 4 of 20%, corresponding to a geometric mean of 1.66 units in the active group (mean 0.51 log units) with a two-sided alpha of 0.001.

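### Cough duration is sized as a comparison of log means but tested by Cox regression, which has about 84% rather than 90% power under the plan's own assumptions and does not yield a percentage reduction

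*Protocol article*

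**What the plan says.** Under Sample size calculation, the protocol expects both primary outcomes to be positively skewed, and so "sample size calculations are based on the log-normal distribution". Cough duration is "estimated as 5.8 (4.1) days" on the raw scale, and "this corresponds to 1.555 (SD 0.637) log days (or geometric mean of 4.74 days) for the cough duration outcome". The target is a 20% lower geometric mean (3.79 days, 1.333 log days). This gives 174 analysed per arm for 90% power at two-sided alpha 0.05, and 218 per arm randomised after 20% attrition. The same section claims 80% power for both outcomes if only 163 per arm are recruited. Severity is handled in the same way: "0.73 (SD 0.454) on the log scale (or geometric mean of 2.08) for the symptom severity outcome", with 89% power at two-sided alpha 0.001.

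Under Analysis of primary outcomes, duration is compared as follows: "Cox proportional hazards models (adjusting by centre) will be employed to examine differences in time to recovery". Follow-up is censored at 28 days and proportional hazards are checked with Schoenfeld residuals. For severity, "Multiple linear regression models (adjusting for centre) will evaluate the effectiveness of steroids in terms of reducing symptom severity", with the mean of six symptoms as the response. No transformation is mentioned, and none is ruled out.

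The Primary research question asks whether prednisolone reduces duration and/or severity "by at least 20% when compared to placebo treatment".

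**The concern.** For duration, the stated power belongs to a comparison of log means, and that is not the primary test. If durations are log-normal and treatment shortens them by a constant factor, the hazards are not proportional. The log-rank or Cox test then loses efficiency against the log-mean comparison.

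The estimate is affected too. The trial's question is a percentage reduction in days, whereas a hazard ratio is a relative recovery rate. The Rationale for the trial design says that a finding of no effect would make further lower-dose research unlikely to be warranted. A reader drawing that conclusion needs an interval that can be set against a ratio of 0.80, and the hazard ratio alone does not supply one.

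**Working it through.** **Inputs** (Sample size calculation): duration mean 5.8, SD 4.1 days; severity mean 2.3, SD 1.1; ratio 0.80; alpha 0.05 and 0.001; 174 analysed per arm; fallback 163 × 0.8 ≈ 130 per arm.

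**1. The protocol's own figures.** Log-normal conversion: σ² = ln(1 + SD²/mean²), μ = ln(mean) − σ²/2.
- Duration: μ = 1.555, σ = 0.637. Severity: μ = 0.730, σ = 0.454. Both are as stated.
- Power = Φ(δ√(n/2)/σ − z).
- Duration, δ = 0.222, n = 174: Φ(3.25 − 1.96) = 90.2%. Then 174/0.8 = 217.5, so 218 per arm and 436 in total. All reproduce.
- Duration, δ = −ln 0.8 = 0.223, n = 130: Φ(2.82 − 1.96) = 80.6%. This reproduces.
- Severity, δ = 0.22, n = 174: Φ(4.52 − 3.29) = 89.1%. This reproduces.

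**2. Power of the Cox test for duration on the same inputs.**
- Simulation from this log-normal with ratio 0.80 and censoring at 28 days: the log-rank (score) test has 84 to 85% power and the Cox Wald test with Efron ties 83 to 84% at 174 per arm. At 130 per arm the range is about 70 to 73%.
- Analytic check: the log-rank test has efficiency 0.816 relative to the log-mean comparison for a normal shift. With δ = 0.223, at 174: Φ(√0.816 × 3.27 − 1.96) = Φ(0.99) = 83.9%. At 130: Φ(√0.816 × 2.82 − 1.96) = Φ(0.59) = 72.3%.
- Tie handling matters with whole-day durations. A Wald test with Breslow ties falls to about 77% at 174 per arm.
- Only 0.3% of controls would exceed 28 days under this log-normal, so the loss does not come from censoring.

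**3. What the hazard ratio measures.** A 20% shortening gives an average hazard ratio of about 1.37 to 1.38. The true ratio under this log-normal varies over time:

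| Day | Hazard ratio |
|---|---|
| 2 | 1.64 |
| 5 | 1.28 |
| 14 | 1.15 |
| 28 | 1.11 |

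No single hazard ratio corresponds to a 20% reduction.

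**4. Severity, if analysed untransformed.** The active mean is 0.8 × 2.3 = 1.84 and its SD 0.8 × 1.1 = 0.88, so the difference is 0.46.
- At 174 per arm: SE = √((1.21 + 0.7744)/174) = 0.107, and Φ(0.46/0.107 − 3.29) ≈ 84%, against 89% stated. Simulation also gives about 84%.
- At 130 per arm, the raw scale gives about 65 to 67%. The log-scale test gives only Φ(3.91 − 3.29) ≈ 73% with δ = 0.22 (75% with ln 0.8). Much of the gap from the claimed 80% is therefore in the fallback statement itself, whatever the analysis scale.

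**The case against.** Four arguments on the other side carry weight.

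- **Cox may suit the data better than the sizing model does.** The protocol quotes resolution in 50% of patients by 7 days, 75% by 14 days and 90% by 4 weeks. Its log-normal gives 73%, 96% and 99.7%. An exponential with a 7-day median gives 50%, 75% and 94%, and under an exponential a 20% shortening is exactly proportional hazards. A reader might infer that Cox is the wrong model. The documents do not support that: non-proportionality follows only from the sizing distribution, and a Schoenfeld check is planned.
- **Log-scale tests are not robustly better.** With a Weibull of the same mean and SD and the same 20% effect, the log-rank test keeps about 82 to 83% power at 174 per arm, while a t-test on logs falls to about 62 to 63%. Zero durations are also possible, because entry does not require a cough score of 3 or more, and a log-normal model cannot take them. A reader might infer that a log-normal model should replace Cox as primary. That is a debatable trade-off, not a correction.
- **The severity scale is not fixed in the text.** A reader might infer that neither primary analysis is the one the trial was sized for. The protocol never says that the score is untransformed, and the analysis plan, not shown here, may log it. If so, there is no mismatch. Even on the raw scale a percentage can be recovered: 0.46/2.3 = 20%.
- **The practical effect is limited.** Recruitment is complete according to Trial status, and 20% attrition is called conservative. With all 218 per arm analysed, Cox power would exceed 90%.

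All four stand as limits. None removes the mismatch for duration.

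**Conclusion.** The point holds for cough duration. The stated 90% and 80% are correct arithmetic for a log-mean comparison. The named Cox test delivers about 84% at 174 per arm and about 72% at 130 under the same assumptions. Its hazard ratio does not express the percentage reduction that the research question asks about.

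These figures assume the sizing log-normal, a constant 20% shortening, no gain from covariate adjustment, and a score test or Efron ties. The loss is moderate: about 6 points at the planned size and 8 at the fallback. It does not show that the trial is badly underpowered or that Cox must be dropped.

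For severity the point is conditional on an untransformed analysis: about 84% against 89% at 174 per arm. The severity shortfall at the fallback should not be attributed mainly to the choice of scale.

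**What to change.** - **Duration:** keep Cox as the primary test. State its power under the sizing assumptions as about 84% at 174 per arm and about 72% at 130. Prespecify a supplementary time ratio with a 95% confidence interval to read against 0.80, for example from a centre-adjusted accelerated failure time model with the same censoring, its distribution checked against the data, and a stated rule for zero durations.
- **Severity:** state the analysis scale. If the score is untransformed, give power at alpha 0.001 as about 84% at 174 per arm and report the difference also as a percentage of the control mean. If it is logged, report the geometric-mean ratio; the 89% then stands.

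The cost is some wording, a slightly less favourable stated power and one extra model on data already collected. The extra model adds a distributional assumption, which is acceptable for a supplementary estimate.

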### Treatment allocation, concealment and emergency unblinding

The computer-generated randomisation schedule will be produced by a statistician who is independent of the OSAC trial statisticians, and stratified by centre using a variable block size. The schedule will be held by the Pharmacy of the University Hospitals Bristol NHS Foundation Trust (“the Pharmacy”), who will allocate medicine packs containing active and placebo tablets and identified by a unique Medicine ID number, to identical, sequentially numbered Patient Packs identified by a unique Participant ID number, which will then be sealed. Packs, which are indistinguishable between active and placebo groups, are issued sequentially to eligible, consented patients at recruiting primary care sites. Clinicians, patients and all members of the research team were masked to the randomisation sequence, and all outcome data were gathered masked to allocation status.

The use of distinct Participant ID and Medicine ID numbers will enable flexibility in the number of patients recruited at each of the four trial centres. Medicine packs can be combined with patient packs as needed, allowing for temporary differential fluctuations in recruitment rates between centres. The four centres will be provided with Patient Packs to distribute to the participating primary care sites in blocks of four (although larger numbers of packs will be issued to practices with proven capacity to recruit to this trial).

The Pharmacy will hold the master drug allocation log and provide a 24 hour emergency unblinding service based on a standard operating procedure for breaking the code in the event of a medical emergency. Trial participants will be given a Trial Participation Card with details of who their Responsible Clinician should contact in the event of an emergency, and all practice-based clinicians will receive training in the use of the emergency unblinding service.

At the end of the trial, the code-break will only be released to the investigative team once written confirmation has been received that primary outcome data analysis is complete.

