#### Analysis of secondary outcomes

The secondary outcomes listed above (see “Secondary outcome measures”) will be analysed using appropriate regression models and will adjust for the baseline measure of the outcome, where possible, and centre.

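### Both primary models fix only centre and choose further covariates by chance baseline imbalance, so baseline symptom severity is not pre-specified and precision is forgone

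*Protocol article*

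**What the plan says.** All references are to the protocol article.

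- **Cough duration** (Analysis of primary outcomes): "Cox proportional hazards models (adjusting by centre) will be employed to examine differences in time to recovery".
- **Symptom severity, days 2 to 4** (same section): "Multiple linear regression models (adjusting for centre) will evaluate the effectiveness of steroids in terms of reducing symptom severity".
- **Further covariates** (same section): "For both primary outcomes models will also adjust for any covariates demonstrating imbalance between the groups at baseline". The article gives no candidate list and no definition of imbalance, and does not label this a sensitivity analysis. Sensitivity analyses are introduced only in the paragraphs that follow.
- **Secondary outcomes** (Analysis of secondary outcomes): the models "will adjust for the baseline measure of the outcome, where possible, and centre".
- **Baseline data**: the factors to be explored for missingness include "values of primary and important secondary outcome variables at baseline" (Analysis of primary outcomes). At the recruitment interview the clinician is to "collect the remaining CRF data (including symptoms, signs and respiratory history") (Trial entry).
- **Randomisation** is "stratified by centre using a variable block size" (Treatment allocation, concealment and emergency unblinding), so centre is rightly in the models.

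**The concern.** In a properly randomised trial any baseline imbalance is chance. Its observed size says nothing about whether the covariate predicts the outcome. A rule that admits covariates because they look unequal can bring in a variable that predicts nothing and leave out a strong predictor that happens to be balanced.

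Two things are at stake. First, the content of the two models that decide the trial depends on the observed data, which invites challenge. Secondary outcomes, by contrast, have their baseline adjustment fixed in advance. Second, precision is forgone. Adjusting for a prognostic baseline reduces residual variance whether or not the arms differ on it. This matters most for severity, which is tested at an alpha of 0.001. A definition of imbalance in a statistical analysis plan would make the rule reproducible, but would not make it select on prognosis.

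**Working it through.** **Inputs** (Sample size calculation, unless noted)
- Severity: mean 2.3, SD 1.1; log-scale mean 0.73, SD 0.454; active-arm log mean 0.51, so the difference is 0.73 − 0.51 = 0.22; two-sided alpha 0.001.
- Cough duration: log-scale mean 1.555, SD 0.637; active-arm log mean 1.333, so the difference is 0.222; two-sided alpha 0.05; 90% power.
- Numbers analysed per arm: 174. For the slower-recruitment scenario, 163 × 0.8 ≈ 130.
- Correlation r between baseline and day 2-4 severity: **not in the document**; assumed 0.3 to 0.6.

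**Step 1. Reproduce the protocol's figures.**
- Log-scale SD for severity: √ln(1 + (1.1/2.3)²) = 0.454. Log-scale mean: ln 2.3 − 0.454²/2 = 0.730. Both agree.
- Cough: n = 2(1.960 + 1.282)² × 0.637²/0.222² = 173.02, rounded up to 174; 174/0.8 = 217.5, rounded up to 218. Both agree.
- Severity power = Φ(0.22/(0.454√(2/174)) − 3.291) = Φ(4.520 − 3.291) = 89.1%, against the stated 89%. A t-based calculation gives 88.4%.

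**Step 2. Always adjust for baseline severity.** The residual SD becomes 0.454√(1 − r²), with the same power formula:

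| r (assumed) | Residual variance | Power, 174 per arm | Power, 130 per arm | n per arm for 89% power |
|---|---|---|---|---|
| unadjusted | 1.00 | 89.1% | 73.1% | 174 |
| 0.3 | 0.91 | 92.6% | 79.0% | 159 |
| 0.4 | 0.84 | 95.0% | 83.5% | 146 |
| 0.5 | 0.75 | 97.3% | 88.9% | 131 |
| 0.6 | 0.64 | 99.1% | 94.4% | 112 |

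For example, at r = 0.5 and 174 per arm: 4.520/√0.75 = 5.219, and Φ(5.219 − 3.291) = 97.3%.

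The unadjusted 73.1% at 130 per arm is below the 80% that the protocol states for both outcomes in that scenario. That is a separate matter: it does not arise from the choice of covariates.

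**Step 3. Does the imbalance rule recover the gain?** This was simulated with 15,000 runs per setting and 174 per arm. Baseline was added only if the arms differed on it at p < 0.05. That threshold is an assumption, as the article gives none.

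| r (assumed) | Power at alpha 0.001: never / always / if imbalanced | Type I error at nominal 5%: never / always / if imbalanced |
|---|---|---|
| 0.3 | 87.9 / 91.9 / 88.3% | 5.0 / 4.9 / 4.8% |
| 0.5 | 88.2 / 96.9 / 89.2% | 4.9 / 4.8 / 4.2% |
| 0.7 | 88.2 / 99.8 / 90.0% | 5.1 / 4.8 / 3.5% |

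The result is as expected. With that trigger, baseline severity enters in only about 5% of randomisations, however prognostic it is. In the remaining 95% the unadjusted standard error is used although the arms are known to be balanced. It is then too large for the estimate it accompanies, which explains the conservative error rate.

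**Step 4. Cough duration.** No gain was computed for the Cox model. The outcome has no direct baseline value. The variance formula above does not carry over either, because adding a covariate to a Cox model changes the hazard ratio being estimated as well as its standard error.

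**The case against.** The strongest replies, and what stands of each:

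- **Baseline severity is not excluded.** This is correct. A reader might infer that the primary models leave it out, but the text lets it in if it is judged imbalanced. The accurate statement is that it is not fixed in advance.
- **This is detail for the analysis plan.** It stands in part. The candidate list and the threshold could be set there, and the sentence might be read as describing an additional model. But the article states the selection rule itself, for both primary outcomes and with no supporting label, and no threshold would cure it.
- **The analysis is blinded.** The code-break is released only after the primary analysis is confirmed complete, which limits steering towards a wanted answer. Imbalance must still be judged from the coded groups, so the model remains data-dependent.
- **The covariate is partly inferred.** This stands. The article does not say outright that the six items are scored 0 to 6 before randomisation. Day 1 is trial entry, the diary is issued with the medicines, and tablets are recorded from day 1, so a day 1 diary score could be post-dose. Adjusting for it could remove part of the treatment effect.
- **The contrast with secondary outcomes is qualified.** Their baseline adjustment applies where possible, and several of them have no natural baseline.
- **Nothing stated is wrong.** This is correct. A reader might infer an inflated false-positive rate or an inadequate sample size, and neither is supported. The simulated rule was conservative, its power was never below that of the unadjusted analysis, and the planned power assumed no covariate gain.

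**Conclusion.** The point holds as a free improvement. The protocol commits both primary models to covariate selection by observed imbalance, and does not fix in advance the baseline measure most likely to be prognostic.

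For severity the forgone power is about 4 to 10 percentage points at 174 per arm (89.1% to 92.6-99.1%) and about 6 to 21 points at 130 per arm (73.1% to 79.0-94.4%). These figures are illustrative. They rest on an assumed correlation of 0.3 to 0.6, on the log scale of the sample size section, and on a usable pre-dose baseline score. The finding that the imbalance rule recovers little also rests on the assumed p < 0.05 trigger.

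It would be tempting to say that precision is lost by a known amount on both primary outcomes. The documents do not support that: the gain for cough duration is unquantified, and the case there rests on the data-dependence of the model.

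**What to change.** Replace the imbalance sentence with a covariate set fixed before unblinding. Because the code-break follows the primary analysis, this should preferably be done before any comparison of the coded groups.

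- **Severity model:** centre and the baseline mean symptom score, defined as pre-randomisation and pre-dose.
- **Cox model:** centre and the pre-dose baseline cough score; optionally prior duration of illness, which the subgroup section already uses.
- **Sensitivity analysis only:** any model that adds covariates because they appear imbalanced.

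Confirm from the case report form that the baseline symptom items are scored and recorded before the first dose. If so, the cost is a change of analysis wording. Recruitment is already complete, and no new data or change to the sample size is needed.
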